### Interim analysis

The project is a pilot trial and interim analysis is not planned. The adverse effects will be reported and communicated to the Ethics Committee.

## Methods: Oversight and monitoring

### Composition of the coordinating center

The principal investigator will bear the responsibility for the overall management of the study. Additionally, the study executive committee, comprising the principal investigator and project coordinator, who is affiliated with Hospital São Rafael (Brazil), will oversee the study’s execution.

#### Composition of the data safety monitoring committee, its role, and reporting structure

This study will undergo monitoring by the local Ethics Committee. Any adverse effects deemed frequent or situations that may cause discomfort to the patient or their representatives will be promptly reported to the Ethics Committee for further evaluation.

#### Adverse event reporting and harms

Serious adverse events (SAEs) encompass various potential outcomes, including arrhythmia, intestinal ischemia, and acute extremity ischemia. These events tend to occur more frequently when administering exceedingly high doses of vasopressors, particularly among patients with an imminent prognosis of death within a few hours or those already exhibiting arrhythmias. Consequently, such cases are excluded from the study. Given the anticipated higher mortality rates within this patient cohort, instances of death are not reported as SAEs in this context.

Furthermore, each type of SAE and the total number of SAEs will be reported in the REDCap database and do not have to be reported separately.

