### Data management

Each patient will be registered in the database at a dedicated website (https://www.project-redcap.org) by the research team. Regular screening of the website for missing and incorrect data will be conducted by the project leader. All collected data will be accessible via the Zenodo repository (https://zenodo.org).

Additionally, all data collected will be included in the collection form.

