#### Frequency and plans for auditing trial conduct

Monitoring will be conducted following national requirements to ensure the protection of patients’ rights and safety, as well as compliance with the protocol, proper data collection, and accurate outcome reporting. The data monitoring process will encompass various aspects, including the inclusion rate, adherence to informed consent procedures, completeness of trial and investigators’ main documents and files, recording of endpoints and SAE reports, and verification of source data such as hospital medical records, medical notes, laboratory findings, and electronic data.

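### Three sections give inconsistent rules on which serious adverse events reach the Ethics Committee, and a single one need not be reported promptly

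*Protocol article*

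**What the plan says.** Three places in the protocol article deal with the reporting of harms.

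- *Interim analysis*: "The adverse effects will be reported and communicated to the Ethics Committee". No condition on seriousness, frequency or timing is attached.
- *Composition of the data safety monitoring committee, its role, and reporting structure*: "This study will undergo monitoring by the local Ethics Committee". It then gives a conditional trigger: "Any adverse effects deemed frequent or situations that may cause discomfort to the patient" (or to the patient's representatives) "will be promptly reported to the Ethics Committee for further evaluation".
- *Adverse event reporting and harms*: arrhythmia, intestinal ischaemia and acute extremity ischaemia are given as examples of SAEs. SAE types and the total count "will be reported in the REDCap database and do not have to be reported separately". Because high mortality is expected in this cohort, "instances of death are not reported as SAEs in this context".

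On who looks at the records, *Data management* states: "Regular screening of the website for missing and incorrect data will be conducted by the project leader". The auditing section lists "recording of endpoints and SAE reports" among the items to be monitored. 28-day mortality is a secondary objective under *Study outcome*.

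**The concern.** The study raises MAP stepwise in patients with septic shock. It plans no interim analysis, and the local Ethics Committee stands in for a data safety monitoring committee. What that committee is told, and when, is therefore the main external protection for participants.

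An investigator who sees one acute extremity ischaemia during a session finds three answers: tell the committee, tell it promptly only if such effects are frequent or the situation causes discomfort, or enter it in REDCap and send nothing further. Two investigators could act differently and each cite the protocol. At stake is whether a first serious event, possibly linked to the induced pressure changes, is seen from outside before more patients are studied.

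**Working it through.** No statistical calculation decides this point. The check is to set the sections side by side.

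**1. Do the sections concern the same events?** Yes, on a plain reading. SAEs are a subset of adverse effects. *Data collection and management* also says the session is interrupted if any adverse effect described later in the text occurs. The only events described later are those given as SAE examples in *Adverse event reporting and harms*. Adverse effects and SAEs are thus not separate classes with separate rules.

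**2. What does each section require for one isolated SAE?**

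- *Interim analysis*: it is communicated to the Ethics Committee, with no timing given.
- *Data safety monitoring committee* section: prompt report only if the effect is judged frequent or the situation may cause discomfort. One event is not frequent in any ordinary sense, and the term is not defined. The discomfort limb might apply, but that is left to judgement.
- *Adverse event reporting and harms*: REDCap entry, with no separate report needed.

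The second and third rules sit close together. Both allow an isolated SAE to go without a prompt report. The first stands apart from them.

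**3. Does REDCap entry itself inform the committee?** The article does not say so. Database screening belongs to the project leader and is aimed at missing and incorrect data. The auditing section covers whether SAE reports are recorded, which is not a review of safety. The executive committee consists of the principal investigator and the project coordinator. No safety body outside the study team is named other than the Ethics Committee.

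**4. Are deaths part of the inconsistency?** No. Neither the interim analysis section nor the data safety monitoring section mentions deaths. The exemption in *Adverse event reporting and harms* is a separate matter. It covers every death, with no limit on timing or relatedness, so it would include one during the session. Such a death is still within the 28-day mortality objective, but nothing routes it to the committee as a possible harm.

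**5. Scale, for context only.** At the stated minimum of 40 patients, one event is 1/40 = 2.5%. If no events were seen, the one-sided 95% upper bound would be 1 − 0.05^(1/40) = 7.2%. These figures hold for any study of 40 and do not establish the inconsistency. They only show that an isolated event is not negligible in a study of this size.

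**The case against.** The strongest reply is that the sections can be read as layers: REDCap is where SAEs are captured, adverse effects are communicated to the committee at some point, and certain situations are sent promptly. The REDCap sentence waives separate reports. It does not forbid them, and it names no recipient. An investigator who enters an SAE in REDCap and also tells the committee breaks none of the rules. This part of the objection stands. A reader might infer that SAEs go to REDCap only, or that the rules cannot all be obeyed together, and the text does not support either inference. What the layered reading leaves unsettled is the minimum an investigator must do for one serious event, and when.

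The discomfort limb also counts. Limb or intestinal ischaemia, or an arrhythmia that stops the session, could plausibly meet it without any frequency threshold. It would therefore be wrong to say that the prompt-report trigger could never fire for a single event. But whether a serious event leads to a prompt report should not depend on whether someone judges it a discomfort.

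A reader might also infer that deaths go unrecorded. They do not, because 28-day mortality is an objective, and the protocol gives a reason for the SAE exemption.

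Other safeguards exist: the session is interrupted when an adverse effect occurs, patients with unstable acute arrhythmia or imminent risk of death are excluded, and SAE records and source data are monitored. These protect the individual patient and the quality of the data. They do not bring an event to an external reviewer.

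Finally, a condensed article may leave SAE forms and timelines to the full protocol. That would answer a complaint about missing detail. It does not answer three stated rules that differ.

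**Conclusion.** The concern holds as an inconsistency between three stated reporting rules. Under the data safety monitoring section and the adverse event section, one SAE during the MAP session need not be promptly reported to the Ethics Committee, although the interim analysis section says adverse effects are communicated to it. The conclusion assumes that SAEs count as adverse effects and that the committee has no access to REDCap beyond what the article describes.

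The consequence is for participant oversight and harms reporting. It does not touch the primary outcome, the analysis or any estimate. The change is worth making because it is specific and cheap and concerns safety.

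The blanket exemption for deaths is a secondary gap, not a contradiction.

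**What to change.** Reconcile the three sections into one rule and state it in the same terms in each: every SAE is entered in REDCap and is also reported promptly to the Ethics Committee. Remove the waiver of separate reports for SAEs, and state that the frequency condition in the data safety monitoring section does not apply to serious events. It can remain as a trigger for non-serious effects.

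Separately, add that a death during the session is communicated to the committee. The investigators may wish to state a short window after the session to which the same applies. Expected later deaths can remain outside SAE reporting and be counted under 28-day mortality.

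The cost is a few sentences of protocol wording and, in a study planned for at least 40 patients, probably a few extra reports. No change to the data collected, the sample size or the analysis is needed.

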#### Frequency and plans for auditing trial conduct

Monitoring will be conducted following national requirements to ensure the protection of patients’ rights and safety, as well as compliance with the protocol, proper data collection, and accurate outcome reporting. The data monitoring process will encompass various aspects, including the inclusion rate, adherence to informed consent procedures, completeness of trial and investigators’ main documents and files, recording of endpoints and SAE reports, and verification of source data such as hospital medical records, medical notes, laboratory findings, and electronic data.

#### Plans for communicating important protocol amendments to relevant parties

Relevant protocol modifications will be communicated to Ethics Committees and ClinicalTrials.org by the principal investigator via email.

#### Research ethics approval

The local Ethics Committee of São Rafael Hospital approved this multicenter study on the 18th of February 2020 with CAE number: 28134720.1.0000.0048. It was ensured that written informed consent to participate will be obtained from all participants. No deviation from the protocol has been implemented without the prior review and approval of the Ethics Committee.

#### Informed consent

Written informed consent is required from either the patient or their legal representatives before initiating the protocol. It is recommended that written informed consent be obtained as soon as possible after ICU admission if sepsis is suspected so that inclusion can be expedited when the selection criteria are met. This procedure anticipates situations where the patient loses the ability to consent, or their caregiver is absent from the hospital.

Patients or their next of kin can withdraw consent at any time during the study without providing a specific reason. Withdrawal should not influence the standard of care. Patients who withdraw from the study are asked to provide consent for the inclusion of data collected before withdrawal.

#### Additional consent provisions for the collection and use of participant data and biological specimens

No biological specimens will be collected.

#### Access to data

All collected data will be accessible via the Zenodo repository (https://zenodo.org).

#### Dissemination policy: Trial results

After the outcome assessment collection, data will be analyzed within 3 months and presented to all investigators before publication. Confidentiality of the data will be maintained, and we guarantee that for 5 years, they will be made available upon request. Important steps will involve disseminating the obtained results among healthcare professionals, patients, and policymakers to contribute to the enhancement of clinical practice in this setting.

## Abbreviations

ARI: Autoregulation index
B4C: Brain4care
CA: Cerebral autoregulation
CBv: Cerebral blood velocity
CrCP: Critical closing pressure
dCA: dynamic Cerebral autoregulation
ICU: Intensive care unit
ICC: Intracranial compliance
IQRs: Interquartile ranges
MAP: Mean arterial pressure
RAP: Resistance-area product
SAE: Serious adverse event
TCD: Transcranial Doppler
